#### Analysis for aim 2b: Mean systolic BP will be lower among patients in the CHPS compounds randomized to the PF strategy than those in usual care at 12 months post-randomization

This analysis will be accomplished using a similar analytic strategy as described for the quantitative analysis for aim 2a. However, in this analysis, the measurements will be taken at the level of the patient rather than the CHO. We will specify a generalized linear multilevel mixed model with fixed effects for time, intervention, and intervention by time. Random effects will be specified for CHPS, CHO, and patient, accounting for measurements clustered within patient, patients clustered within CHO, and CHOs clustered within CHPS. SBP will be measured as a continuous variable in mmHg at baseline and 12 months for all patients. Multilevel modeling software (SAS, version 9, PROC MIXED) will be used to compute full information maximum likelihood (FIML) estimates of the model parameters for the fixed and random effects.

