### Sites and participant recruitment

Participants will be recruited from eligible CHPS zones that (1) have at least 2 community health workers (CHWs) employed in the CHPS program and (2) are certified as a National Health Insurance Scheme provider. A total of 70 CHPS zones will be recruited into this trial.

Patients for the study are identified from the CHPS zones by the CHWs during provision of their routine services and visits with families or through of the conduct of health fairs in participating CHPS zones. Each zone is expected to recruit consent 10 consecutive patients who meet the eligibility criteria below. Study coordinators will obtain individual consent from eligible patients before they can be enrolled in the study. For patients recruited to the CHPS zones, once eligibility is confirmed, all patients regardless of their group assignment will have a total of four study visits: baseline, 6 months, 12 months, and 24 months post-randomization. The structure of each study visit and the respective measures will be the same for each group. A total 70 CHPS compounds and 700 patients will be enrolled in this study with approximately 10 patients per CHPS compound. Patients may withdraw from or refuse to participate in the trial at any point, and it will not affect the clinical care they receive.

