#### Blood pressure measurements

The systolic BP reduction in patients will assessed as follows as mean change in systolic BP from baseline to 12 months. BP readings will be assessed with validated automated BP device as we did in our previous trial [10]. A total of three readings will be taken by trained study coordinators using an automated BP monitor with the patient seated comfortably for 5 min prior to the measurements, following the AHA guidelines [31]. The same procedure will be followed at 6- and 12-month study visits. The average of the 3 BP readings will be used as the measure for each study visit. Uncontrolled BP is defined as average clinic SBP ≥ 140 mmHg or DBP ≥ 90 mmHg following JNC-7 guidelines [31].

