
#### Analysis for aim 2a: The adoption of TASSH will be higher in the CHPS compounds randomized to the PF strategy than those in usual care at 12 months post-randomization

This analysis will be accomplished with a multilevel mixed model using an unstructured covariance matrix across two time points, baseline and 12 months. The analysis will have one within-person factor—time (baseline and 12 months coded naturally as months 0 and 12)—and one primary between-patient factor (randomization group dummy coded as 0 = UC and 1 = PF). Fixed effects will be specified for time, randomization group, and their interaction effect (group by time). The outcome measure will be a composite index for adoption of TASSH (defined as rate of identification of HTN, rate of lifestyle counseling for patients with HTN, and medication referral for patients with HTN). Additionally, the CHOs will be nested within compounds creating a 3-level analytic model (observations nested within CHOs nested within compounds). Random effects will be specified for CHPS and for CHO, adjusting for the clustering of measures within CHO and CHO within CHPS. Multilevel modeling software (SAS, version 9, PROC MIXED) will be used to compute full information maximum likelihood (FIML) estimates of the model parameters. The PROC MIXED procedure will use an error structure that allows for the possibility of group differences in (a) the error variances at 12 months and (b) the serial correlations of the baseline with the 12-month outcomes. The primary test is the group × time interaction, and the resulting *F* test will provide the primary “intent to treat” test of the hypothesis. If this is statistically significant at the two-tailed *α* = .05 level, for ease of interpretation, we will estimate and report the magnitude of the treatment effect, with 95% CI for adoption. Ideally, the randomization of participants to treatment groups will obviate the need for any covariates in the analysis. However, in the event that baseline differences between the patients in each group on the outcomes, demographic, or secondary measures are found, those variables will be included as covariates in the model (including their interactions with time).

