#### Consideration of missing data

Although longitudinal designs tend to have missing data due to attrition, we anticipate very little missing data for the adoption ratings as these will come from the staff at the CHPS compounds. For the SBP data, there may be more missing data as these data will be obtained from patients. Using the maximum likelihood multilevel modeling approach to estimate treatment effects, we will include data from all the staff and patients who are enrolled in the trial (intent-to-treat) even if some of the patients’ data are missing. Maximum likelihood estimation, a technique which utilizes observed data to generate parameter estimates for all participants in an intent-to-treat design, has been found to be a useful method for dealing with participant attrition and missing data in clinical trials [42].

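### The SBP model omits the 6-month reading, and the arm comparisons in aims 2a, 2b and 3 are change-score contrasts that adjust for baseline only if imbalance is found

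*Protocol article*

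**What the plan says.** **Visits.** Sites and participant recruitment schedules every patient at "baseline, 6 months, 12 months, and 24 months post-randomization". Blood pressure measurements describes three automated readings per visit and adds: "The same procedure will be followed at 6- and 12-month study visits". The SBP outcome is the "mean change in systolic BP from baseline to 12 months".

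**Aim 2b model.** Only two of these visits are named: "SBP will be measured as a continuous variable in mmHg at baseline and 12 months for all patients". The fixed effects are time, arm and their interaction, with random effects for compound, CHO and patient.

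**Aim 2a model.** This is a "multilevel mixed model using an unstructured covariance matrix across two time points, baseline and 12 months", with the same three fixed effects. "The primary test is the group × time interaction". Aim 3 repeats the form with 24 months in place of 12.

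**Baseline covariates.** The aim 2a section adds covariates, outcomes included, only when the arms are found to differ at baseline.

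**Missing data.** Consideration of missing data warns: "For the SBP data, there may be more missing data as these data will be obtained from patients". It relies on maximum likelihood with all enrolled staff and patients kept. No dropout rate, baseline-to-follow-up correlation or SD is given.

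**The concern.** Two separate choices leave collected information unused.

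The first is the form of the test. With two visits and arm means free at both, the interaction is the difference between arms in mean change. It gives baseline a fixed weight of one, where adjustment would estimate the weight. Adjusting only after imbalance has been seen does not repair this: the precision gain does not depend on observed imbalance, and a data-dependent covariate rule is not a prespecified model. At stake are wider intervals than the data allow, including for the primary outcome, where planned power is only just .80.

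The second is the missing 6-month SBP. A patient seen at month 6 and then lost enters the likelihood with a baseline value alone. If leaving depends on the 6-month BP, the model has not conditioned on what drove the loss, and the 12-month difference can be biased. This applies only to SBP, a secondary outcome; no 6-month adoption rating is described.

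**Working it through.** **1. The plan's own figure.** Inputs from Sample size and power estimates: d = .50 on change, α = .05 two-sided, power .80, ICC .10, 2 CHOs per compound.
- n per arm = 2(1.960 + 0.842)²/0.50² = 62.8, so 63.
- Design effect = 1 + (2 − 1)(.10) = 1.1. 63 × 1.1 = 69.3 CHOs per arm, so 35 compounds per arm and 70 in all. The figure reproduces.
- Effective n per arm = 70/1.1 = 63.6. Power is .805 (normal) or .794 (t, 68 df).
- SBP with 10 patients per compound: design effect 1.9, effective n 350/1.9 = 184, power .998 at d = .50. The detectable d at 80% power is about .29.

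**2. Baseline adjustment, equal SDs, no clustering.** Change-score variance is proportional to 2(1 − ρ) and adjusted variance to 1 − ρ². Their ratio is (1 + ρ)/2, so the share saved is (1 − ρ)/2. All values of ρ are assumed.

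| ρ | .3 | .4 | .5 | .6 | .7 |
|---|---|---|---|---|---|
| saved | 35% | 30% | 25% | 20% | 15% |

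**3. With clustering.** For compound means of m people, the over-time correlation is r = [m·ICC·CAC + (1 − ICC)·IAC]/[1 + (m − 1)·ICC]. CAC and IAC are the over-time correlations of the compound effect and of the individual deviation. Assumed ranges: CAC .6–1.0, IAC .3–.6. ICC is .10.

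| Outcome | CAC, IAC | r | saved |
|---|---|---|---|
| Adoption, m = 2 | .6, .3 | (.12 + .27)/1.1 = .355 | 32% |
| Adoption, m = 2 | 1.0, .6 | (.20 + .54)/1.1 = .673 | 16% |
| SBP, m = 10 | .6, .3 | (.60 + .27)/1.9 = .458 | 27% |
| SBP, m = 10 | 1.0, .6 | (1.00 + .54)/1.9 = .811 | 10% |

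If d = .50 on change is true, power for adoption (.794) would become about .86 with 16% saved and .92 with 32% saved, from the same 140 CHOs.

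**4. Unequal SDs.** With k = SD₀/SD₁₂, the share saved is 1 − (1 − ρ²)/(1 + k² − 2ρk). At k = .6–.7 and ρ = .3–.5 it is 1–15%. The excess variance of the change score is (1 − b)²·Var(baseline), where b is the slope of 12-month on baseline SBP. Entry requires an average systolic BP of 140–179 over two visits. In illustrative simulations (assumed population mean 135, between-person SD 16–20, within-person SD 8–11), the saving was 0.4–1.5% when the screening average served as baseline and 14–24% when baseline was a separate reading.

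**5. Precision from the 6-month reading.** Generalised least squares was run for two-visit and three-visit models, with baseline correlations .3–.5, a 6-to-12-month correlation .1 higher, and half of dropouts seen at month 6 (all assumed). Complete data gave a gain of 0%; dropout of 10–30% gave 0.4–3.8%.

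**6. Bias from dropout linked to the 6-month reading.** All inputs are assumed: SD 18 mmHg, 6-to-12-month correlation .6, baseline correlations .4–.5, 20% dropout per arm, linked to 6-month SBP in usual care only. With the log-odds of dropout rising by .3 to 1.0 per SD, the two-visit likelihood estimates a true 5 mmHg difference as about 4.6 down to 3.6. The three-visit model recovers 5. This one-arm mechanism is an illustration, not a forecast.

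**The case against.** A group-by-time mixed model is a standard, valid analysis. It matches the stated outcome, and the sample size is defined on the same change scale. That stands. A reader might infer that the trial is underpowered; the protocol's figures do not support this, because the 70 compounds give the planned power for the planned test.

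A reader might also take a loss of 25–35% as established. It needs ρ of .3 to .5, equal SDs and no clustering, none of which the protocol states. Nor can the loss be laid on the omitted visit; nearly all of it comes from the change-score form.

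It is tempting to argue that the 140–179 mmHg entry window makes change scores especially noisy. Step 4 shows the reverse: restricting baseline shrinks Var(baseline), and the penalty with it.

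Nor is protection against dropout lost altogether. Full-information maximum likelihood on the planned model still covers dropout that depends on arm and baseline SBP. Only dependence on the 6-month value is left uncovered.

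Finally, forcing a common baseline mean is not free of risk. Zone staff identify the patients, they are not blinded, and the protocol does not clearly place patient enrolment before zone allocation. If selection differs by arm, that constraint can bias the estimate, whereas the planned model lets baselines differ. This stands and limits the fix. It is no reason to make adjustment depend on observed imbalance.

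**Conclusion.** The point holds as a missed, nearly free improvement. The planned analysis is valid and the sample size is consistent with it.

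- **Form of the test (aims 2a, 2b, 3).** Baseline adjustment is asymptotically at least as efficient as the change score. For the 12-month analyses the variance saved is about 16–32% for adoption and 10–27% for SBP, given ICC .10, equal SDs and the assumed over-time correlations. For SBP it falls to near zero if the screening average is the baseline.
- **Omitted 6-month SBP (aim 2b only).** The precision cost is about 0–4% with up to 30% assumed dropout. The more substantive loss is that dropout driven by the 6-month reading is not covered. Its size cannot be fixed from the protocol, which expects missing SBP but gives no rate or pattern.

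The gain matters most for adoption, the primary outcome, where planned power is about .80. For SBP, power at d = .50 is already .998, so the stronger reason to change that model is dropout.

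**What to change.** **Aim 2b.** Model SBP at baseline, 6 and 12 months with categorical time and unstructured within-patient covariance, and test the arm difference at 12 months. To combine this with baseline adjustment, enter baseline SBP as a covariate (with its own slope at each visit) and treat months 6 and 12 as responses.

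**Aims 2a, 2b and 3.** Prespecify adjustment for the baseline outcome (ANCOVA) regardless of observed imbalance, replacing the rule that depends on differences being found. Test the arm difference at 12 months (24 months for aim 3). Keep the compound-level random effects.

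**Common-baseline constraint.** Use it only where baseline was measured, and patients were enrolled, before allocation was known. State the order of enrolment and allocation, and whether baseline SBP is the screening average or a separate reading.

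**Cost.** A few sentences and some code. The 6-month SBP and the baseline values are already scheduled, so no new data are needed and the sample size need not change.

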#### Analysis for aim 3: Sustainability of TASSH will be higher at the CHPS zones randomized to PF than those in CHPS zones randomized to usual care at 24 months post-randomization

Sustainability will be defined as adoption of TASSH at 24 months (12 months following the completion of the intervention). As in aim 2a, this analysis will be conducted at the level of the CHO. The analysis will be accomplished with a multilevel mixed model using an unstructured covariance matrix across two time points, baseline and 24 months post-randomization. Fixed effects will be specified for time, group, and group by time. Random effects will be specified for CHO and CHPS to account for the clustering of measurements.

#### Analysis for aim 4: Inner setting variables (implementation climate, leadership support, organizational capacity) will mediate the effect of PF on adoption of TASSH at 12 months following randomization and sustainability at 24 months following randomization

In this analysis, we will evaluate the mediators of adoption and sustainability of the PF implemented TASSH program. In particular, we will assess the extent to which inner setting variables (e.g., implementation climate, leadership engagement, and organizational capacity) affect the degree of adoption of TASSH at 12 months utilizing structural equation modeling techniques. We will estimate a just-identified path model using the robust weighted least squares estimator to investigate relationships among the theoretical mediators of implementation climate, leadership engagement, and organizational capacity. Based on our conceptual model, we will test the direct effects from the theoretical constructs to adoption. In addition to the direct effects, the indirect effects from the PF intervention to adoption via inner setting variables will be estimated as the product of component direct effects and tested using bootstrapped 95% confidence intervals. As with previous models, random effects will be specified for CHPS and participant to account for the clustered nature of measurements.

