#### Sample size and power estimates

The proposed design is a cluster randomized design to compare PF versus usual care. The primary outcome is a composite measure of adoption ratings to assess the degree to which the TASSH protocol is implemented at the CHPS compounds. The secondary outcomes are the difference in the change in systolic BP between patients at the CHPS sites randomized to PF versus those at the usual care CHPS sites. The unit of randomization is the CHPS compound, and the total sample size is the average number of CHOs at the CHPS sites who will provide the adoption ratings (primary outcome) at each site × the number of CHPS compounds and the average number of patients whose systolic BP will be assessed (secondary outcome) enrolled at each CHPS compound × the number of CHPS compounds. In order to estimate the number of CHPS compounds and the average number of CHOs and the average number of patients needed to have power of .80 for a hypothesis test with a type 1 error rate (alpha) of .05, we have assumed a moderate standardized effect size (*d*) of .50 of the difference in change in adoption ratings between the CHOs in the CHPS sites in the UC group versus those in the CHPS sites in the PF group from baseline to 12 months. We note that Baskerville et al. reported in a systematic review of practice facilitation in primary care settings an average effect size of *d* = .56 [15]. We also calculated the sample size for an assumed degree of dependency (intra-cluster correlation—ICC) of the CHOs’ data within CHPS compounds of .10. Thus, for an ICC of .10 and 2 CHOs providing the adoption ratings, our target number of CHPS compounds to recruit is 70. As such, a total of 140 CHOs will participate in this study. For the secondary outcome of patient change in systolic BP, we will have substantially greater power than .80 under the same effect size (*d* = .50) and ICC assumptions as we anticipate enrolling an average of 10 patients/compound. So, with 70 compounds, we would enroll 700 patients. Aim 3 concerns the correlation relationship between different mechanisms of change and the change in adoption ratings between baseline and 12 months. For this analysis, we will have the entire sample of 70 compounds and 140 nurses. With this sample and the same assumptions that we made for aim 2a and aim 2b, we will have power of .80 to detect a moderate correlation of .30. Finally, aim 4 concerns detecting a quadratic pattern consistent with sustainability across the baseline and 12- and 24-month time points. Again, the entire sample will be available for this analysis. The standardized effect size for the quadratic effect will depend considerably on the exact form of the quadratic pattern. The largest effect size would occur when the adoption is not sustained; that is when the adoption ratings revert to their baseline values after PF has ended. With the proposed sample size, we will have power greater than .90 to determine if this unwelcome event occurs.

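### The Aim 4 mediation model takes the 12-month level of adoption as its outcome and names no baseline adoption, so the indirect effect can be biased if practice facilitation moves the mediators

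*Protocol article*

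**What the plan says.** The section on the analysis for Aim 4 will assess how far inner-setting variables "affect the degree of adoption of TASSH at 12 months utilizing structural equation modeling techniques". It specifies the form: "We will estimate a just-identified path model using the robust weighted least squares estimator to investigate relationships among the theoretical mediators". It also says that "the indirect effects from the PF intervention to adoption via inner setting variables will be estimated as the product of component direct effects", with bootstrapped 95% confidence intervals. The variables named are PF, the mediators (climate, leadership, organizational capacity) and adoption. No baseline value of adoption or of a mediator is named, and none is ruled out. The section heading extends the question to sustainability at 24 months.

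Three other places bring in baseline:
- The power section, under a label that does not match the list of aims, says: "Aim 3 concerns the correlation relationship between different mechanisms of change and the change in adoption ratings between baseline and 12 months".
- The Aim 2a analysis is "a multilevel mixed model using an unstructured covariance matrix across two time points, baseline and 12 months", so baseline adoption is collected. The Aim 3 model likewise uses baseline and 24 months.
- The study outcomes section classes a CHO as an adopter when all three component rates have risen, which also refers back to an earlier value.

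**The concern.** An indirect effect is the product of two paths: PF to mediator (a) and mediator to adoption (b). Zones are randomized, so baseline adoption can distort a only by chance. Nothing protects b. Compounds that already adopted more may plausibly score higher on climate, leadership and capacity, and may also adopt more at 12 months. If baseline adoption is left out, that standing difference enters b and is then multiplied by a.

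This differs from the question of when the mediators are measured, because earlier measurement would not remove it. It also does not need the arms to be unbalanced at baseline. At stake is the Aim 4 conclusion about which mechanism carries the effect of PF, which is part of what the trial means to offer policymakers for scale-up.

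**Working it through.** **Plan's own figures.** For d = 0.50, power 0.80 and two-sided alpha 0.05, 63 CHOs per arm are needed. The design effect is 1 + (2 − 1) × 0.10 = 1.10, and 63 × 1.10 = 69.3. That gives 70 CHOs or 35 compounds per arm, so the 70 compounds reproduce. The stated power of 0.80 for a correlation of 0.30 does not. Using Φ(atanh(0.30) × √(N − 3) − 1.96), power is 0.72 at N = 70, 0.93 at N = 140/1.10 = 127.3 and 0.95 at N = 140. This does not decide the present point, but the plan's power figure refers to a change outcome.

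**Set-up (assumed).** Let Y0 be baseline adoption, M one mediator and Y12 adoption at 12 months, each with within-arm SD 1.
- M = 0.5·PF + rm·Y0 + error
- Y12 = 0.5·PF + ry·Y0 + error

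There is no M-to-Y12 effect, so true mediation is zero. Neither rm nor ry is in the document; four pairs span a range.

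**Closed form.**
- Level outcome, Y0 omitted: b = Cov(M, Y12 | PF) / Var(M | PF) = rm × ry. The indirect effect is 0.5 × rm × ry. The total effect is 0.5, so the falsely mediated share is rm × ry.
- Raw change Y12 − Y0, Y0 omitted: b = rm × (ry − 1), which is negative whenever rm > 0 and ry < 1.
- Y0 included: b = 0. Subtracting Y0 from the outcome changes only the coefficient of Y0 (by −1), so b is the same for level and change.

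| ry; rm | Level: share rm·ry | Level: indirect (SD) | Change: indirect 0.5·rm·(ry − 1) |
|---|---|---|---|
| .5; .3 | .15 | 0.075 | −0.075 |
| .5; .5 | .25 | 0.125 | −0.125 |
| .7; .5 | .35 | 0.175 | −0.075 |
| .7; .7 | .49 | 0.245 | −0.105 |

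**Simulation, one mediator, 35 + 35 compounds, 400 trials per pair.** Without baseline, the falsely mediated shares were 15%, 25%, 34% and 47%, and the bootstrap interval excluded zero in 13%, 31%, 45% and 55% of trials. With Y0 in both equations, the indirect effect was within 0.004 of zero and false positives were 3% to 5%.

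**Simulation, one mediator, CHO level, 70 × 2 CHOs, ICC 0.10, ry = .5, rm = .3 or .5, 300 trials.**
- PF moves the mediator by 0.5 SD: without baseline, mean indirect effect 0.08 and 0.12, falsely significant in 36% and 68%. With baseline, 0.00, and 4% to 5%. Raw change score, −0.08 and −0.13, falsely significant in 36% and 68%.
- PF does not move the mediator: without baseline, mean about 0.00, and zero excluded in 1% to 4%.

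**Three mediators, compound level.** Assume a mutual within-arm correlation of .6 and the same rm for each. The b for each mediator falls to rm × ry / (1 + 2 × .6) = rm × ry / 2.2. In simulation over the first three pairs, false positives per mediator were about 4–5%, 6–8% and 10–13%. The summed indirect effect was still falsely significant in about 13% to 43% of trials.

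**The case against.** The strongest objection is that this is a condensed article and its silence is being read as a decision. The covariates of a secondary path model often sit in an analysis plan, and none is shown. The Aim 4 section also says that "random effects will be specified for CHPS and participant to account for the clustered nature of measurements", as in the earlier models. A participant effect suggests repeated measurements, and the earlier adoption models included baseline. The study outcomes section can be read as making adoption a change in itself. And no correlation between baseline adoption and the mediators is reported anywhere.

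Much of this stands. A reader might infer that the plan rejects baseline adjustment, but the text does not say so. A reader might also infer that false mediation is bound to appear. It is not: it needs PF to shift the mediator and both correlations to be present, and its sign depends on whether the outcome is a level or a change. Nor do the one-mediator false-positive rates show that climate in particular would be credited wrongly.

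What does not stand is that nothing is left to settle. The article fixes the outcome, model form, indirect effect and interval for Aim 4, and its outcome differs from the one used for power. A random effect for compound or participant models clustering; it does not condition on baseline adoption. The Aim 2a rule for adding covariates is triggered by differences between arms, and this confounding exists in balanced arms too.

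**Conclusion.** The point holds in limited form. As written, the Aim 4 model targets the 12-month level and names no baseline adoption, while the power section and the definition of an adopter point to change. These readings are not reconciled, and without baseline adjustment they can give indirect effects biased in opposite directions from the same data.

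The size is conditional: about 15% to 47% of the total effect falsely mediated in a one-mediator model with zero true mediation, a 0.5 SD effect of PF on both mediator and adoption, and the four assumed correlation pairs. The false-positive rate per mediator is lower with several correlated mediators, though not for their sum. The bias is nil if PF does not move the mediator. The algebra is for a continuous adoption index in linear equations; it was not worked out for the yes/no adopter classification. The comparisons of adoption and systolic BP between arms are not affected.

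**What to change.** In the Aim 4 analysis section, state which adoption outcome is modelled. Include the baseline adoption index as a covariate in each mediator equation and in the adoption equation, at 12 and at 24 months. Add the baseline score of a mediator wherever that scale is collected at baseline. With these paths estimated freely, the model can stay just-identified. For a continuous index, the mediator coefficient is then the same for a level or a change outcome, which reconciles this section with the power section. A raw change score should not be used instead of the covariate, since it can reverse the bias rather than remove it. The aim number in the power section should be corrected at the same time.

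The cost is wording, because baseline adoption is already collected, plus one or more extra coefficients per equation with 70 compounds. Other confounding of the mediator-to-adoption path would remain and should be acknowledged when Aim 4 is reported.
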